**(Zα/2+Zβ)^2^ X [**π**_0_ (1-**π**_0_) +** π**_1_(1-**π**_1_)]**

**n = ___________________________________**

**(**π**_0_-** π**_1_)^2^**

Then, the sample size will be:

**(1.96+0.80)^2^ X [0.79(1-0.776) + 0.876(1-0.876)]**

**n = _________________________________________**

**[0.876-0.776]^2^**

**n**= **245** for each groups

Because, our study is cluster randomized trial, we assumed design effect 1.5 by cluster sampling method to overcome the design effect. Then, the sample size will be:

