## 3.5. Sample Size and Sampling Technique

### 3.5.1. Sample size determination

For cluster level intervention, the sample size is calculated using double population proportion formula for cluster randomized trial [76, 77], with the assumption of the percentage of screening rate (π_0_) at the base line is similar in both groups; and Z_α/2_ the standard normal variable, at α = 5%; Z_β_ is (1-β) = 80%; **π_0_** is the prevalence of the participants who have knowledge about breast self-examination as screening methods since the affordable behavior is BSE (77.6%) [78]; a variable which gives maximum sample size; **π_1_** is the prevalence of screening rate in the intervention cluster/ kebele (87.6%) (Assumed to be increased by 10%); k is coefficient of variation of true proportions of the outcome variable between the clusters within each group. Since there is no study to estimate k, it is taken as 0.25.

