**245*1.5 = 367.5 ≈ 368**

Finally, sample size further increased by 10% to account for contingencies such as non-response or recording error, i.e. 368 X 10/100 + 368= 404.8 ≈ **405**. Therefore, the final sample size will be 405 women for each group. Hence, the total number of study clusters/kebeles will be 30 i.e.15 kebeles in each arm based on WHO cluster sampling recommendation and then proportionally distributed according the number population in the cluster [69].

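### The printed sample-size working gives 218 per group (222 with its two input slips corrected), not the stated 245, so 368 and 405 do not follow from the formula shown

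*Protocol*

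**What the plan says.** Section 3.5.1 of the protocol (Sample size determination) sets out these inputs:

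- Z for α/2 is "the standard normal variable, at α = 5"%, entered as 1.96.
- Zβ is equated in words with 1−β, that is, with 80%.
- The baseline proportion π0 is the prevalence of "knowledge about breast self-examination as screening methods since the affordable behavior is BSE (77.6"%).
- π1 "is the prevalence of screening rate in the intervention cluster/ kebele (87.6%) (Assumed to be increased by 10"%).

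The formula printed next is the unpooled two-proportion formula, (Zα/2 + Zβ)² × [π0(1−π0) + π1(1−π1)] / (π0−π1)². It has no continuity correction. The numerator is then filled in as "1.96+0.80)^2^ X [0.79(1-0.776) + 0.876(1-0.876"), the denominator as 0.10 squared, and the result is given as 245 per group.

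Two inflation steps follow. For clustering, "we assumed design effect 1.5 by cluster sampling method to overcome the design effect", which gives "245*1.5 = 367.5 ≈ 368". Then the "sample size further increased by 10% to account for contingencies such as non-response or recording error", which gives 404.8, and "the final sample size will be 405 women for each group". The total of 810 used in the Summary, the sampling section and the flow chart is twice this.

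**The concern.** Two of the substituted numbers disagree with the inputs stated just above them. The value 0.80 is a probability, the power; the formula calls for the corresponding normal quantile, 0.8416. The sentence defining Zβ makes the same confusion, so this is not a fault of text extraction. And π0 appears as 0.79 in one factor but as 0.776 in its own complement and in the denominator.

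The stated result also does not follow from the line that is meant to produce it. The figure of 245 carries everything after it: 368, 405 and the enrolment of 810. If 245 cannot be derived from the formula shown, a reader, ethics board or journal statistician cannot reproduce the size of the trial. Section 3.9 commits the trial to CONSORT reporting, so the sample-size justification will have to be written up, and as it stands its formula, inputs and result contradict one another.

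**Working it through.** **Inputs (all section 3.5.1):** two-sided α 0.05 (1.96), power 80% (quantile 0.8416), π0 = 0.776, π1 = 0.876, difference 0.10, design effect 1.5, 10% inflation applied as × 1.10, equal groups.

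**1. The line exactly as printed**
- (1.96 + 0.80)² = 7.6176
- 0.79 × 0.224 + 0.876 × 0.124 = 0.17696 + 0.108624 = 0.285584
- n = 7.6176 × 0.285584 / 0.01 = 217.5, so 218. The plan states 245.

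**2. Printed formula, 0.776 in both places, 0.80 kept**
- 0.776 × 0.224 + 0.108624 = 0.173824 + 0.108624 = 0.282448
- n = 7.6176 × 0.282448 / 0.01 = 215.2, so 216

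**3. Printed formula, both slips corrected**
- (1.96 + 0.8416)² = 7.8490
- n = 7.8490 × 0.282448 / 0.01 = 221.7, so 222

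The 0.79 moves the result by about 1%. Correcting both inputs moves it only from 217.5 to 221.7. The gap to 245 remains.

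**4. A formula that does give 245**
- Pooled proportion: (0.776 + 0.876)/2 = 0.826; 2 × 0.826 × 0.174 = 0.287448
- Pooled-variance n = (1.96 × √0.287448 + 0.8416 × √0.282448)² / 0.01 = 224.4
- Continuity correction: (224.4/4) × [1 + √(1 + 4/(224.4 × 0.10))]² = 244.02, rounded up to 245

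Pooled variance without the correction gives 225. One-sided versions give 177, or 197 with continuity correction. At 90% power the formulas without correction give 297 to 300. None of these matches.

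**5. The later steps**

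| Starting n | × 1.5 | × 1.10 | per group | total |
|---|---|---|---|---|
| 245 (stated) | 367.5 → 368 | 404.8 | 405 | 810 |
| 222 (printed formula, corrected inputs) | 333 | 366.3 | 367 | 734 |
| 218 (line as printed) | 327 | 359.7 | 360 | 720 |

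The steps from 245 onward are correct; the fault lies in reaching 245. The stated 405 is about 10% above what the printed formula supports with correct inputs (405/367 = 1.10).

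**6. Power at the stated size**

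With 368 women per arm after losses and a design effect of 1.5, the effective number is 368/1.5 ≈ 245.
- Standard error = √(0.282448/245) = 0.03395; 0.10/0.03395 = 2.945
- Normal approximation: Φ(2.945 − 1.96) = 0.838, about 84%
- t with 30 − 2 = 28 df: about 81%

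For comparison, reading 0.80 as a normal quantile corresponds to 78.8% power.

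**The case against.** The strongest reply is that nothing is lost. The stated 245 exceeds both 218 and 222, the later steps are right once 245 is accepted, and the same α, power, π0 and π1 do give 245 under a recognised method. On that view this is a typesetting matter in the working.

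Much of this stands, and it limits the point:

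- A reader might infer that the trial is underpowered by this error. It is not; the error runs in the safe direction.
- A reader might infer that 405 is too many for the plan's assumptions. It is too many only for the printed formula, since the same assumptions give 245 with pooled variance and continuity correction.
- A reader might take the two substitution slips as the cause of the discrepancy. They account for about four women per group; the gap from 222 to 245 has another source.
- A reader might take the continuity-corrected formula as the sponsor's method. The numerical match is good, but section 3.5.1 mentions neither a pooled variance nor a continuity correction, so this remains conjecture.
- A reader might fear a conflict with a registered sample size, with a later re-estimation, or with a fixed number of women per kebele. The protocol gives a registration number but no registered size, plans no re-estimation, and distributes women in proportion to kebele population.

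What does not stand is the suggestion that the working can be left alone. The protocol states the calculation itself, so this is not a detail left for an analysis plan, and no other section supplies a different derivation.

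**Conclusion.** The sample-size working in section 3.5.1 is wrong as written. It contains two incorrect inputs, and the stated result does not follow from the formula shown whether or not those inputs are corrected: 218 as printed, 222 corrected, 245 stated. Carried through, the corrected printed formula supports 367 per group (734 in total) against the stated 405 (810). This is a failure of reproducibility, not of power.

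The power figures of about 84% and 81% rest on the plan's own π0, π1 and design effect of 1.5, taken at face value. Whether those assumptions are adequate is a separate matter that this point does not address.

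**What to change.** In section 3.5.1, define Zβ as the normal quantile for 80% power (0.8416) and use 0.776 for π0 in both places. Then do one of two things:

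1. If the sponsor confirms that 245 came from the pooled-variance formula with continuity correction, print that formula, its substitution and its result (244.02, rounded up to 245). It should not be printed as the derivation without that confirmation, because that could document a calculation that was never made.
2. Otherwise keep the printed formula, state 222 per group (333 after the design effect, 367 after the 10% inflation), and present 405 per group as a deliberately larger size, giving its power under the stated assumptions.

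Either way the change is to protocol wording only. Enrolment stays at 810.

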**245*1.5 = 367.5 ≈ 368**

Finally, sample size further increased by 10% to account for contingencies such as non-response or recording error, i.e. 368 X 10/100 + 368= 404.8 ≈ **405**. Therefore, the final sample size will be 405 women for each group. Hence, the total number of study clusters/kebeles will be 30 i.e.15 kebeles in each arm based on WHO cluster sampling recommendation and then proportionally distributed according the number population in the cluster [69].

### Sampling techniques and procedure

Hadiya zone has twelve districts (ten woredas and two city administrations). For sampling, in phase 1, ideally sample size for qualitative research depends on data saturation. For now, six focus group discussions proposed to be conducted with women and nine in-depth interviews will be conducted with health workers in selected six districts. Phase 2, we will select six districts randomly by multistage cluster random sampling method. Then, we will select 30 kebeles from the selected districts and we will evenly distribute in intervention and control groups (i.e. 30 kebeles will be divided into 15 control and 15 intervention groups). To prevent information contamination, random assignment will be used to make control and interventional sites are far from each other. As shown in figure 2 below, we will divide 810 participants proportionally for each selected clusters/kebeles. Hence, the total number of study clusters will be 30 i.e.15 clusters/kebeles in each arm based on WHO cluster sampling recommendation [69].

**Twelve districts (Ten Woredas and two city administration in Hadiya Zone, Southern Ethiopia)**

**Six districts (Four woredas and two city administration (30 kebeles) = 810 women participants)**

**0**

**Three districts (Two Woredas and one city administration in control arm (15 kebeles))**

**Three districts (Two districts and one city administration in intervention arm (15 kebeles))**

**405 samples for control arm from each district accordingly**

**405 samples for intervention arm from each district accordingly**

# Fig 2. Schematic presentation of sampling procedure

### 3.5.2. Recruitment plans

For the participant enrollment, in phase 1 qualitative data will be collected from women, heath extension workers, medical directors and disease prevention and control officers. In phase 2, women who are potentially eligible for the study will be listed, and each individual will be invited to participate in the study through oral invitation or phone call performed by principal investigator and health extension workers of each selected kebeles/clusters. An appointment will be made if the person agrees to participate. Following an oral informed consent, women will be included for eligibility as subjects of the study by a research member, baseline data will be obtained, and participants will be allocated either intervention or control group. Written informed consent will be obtained from the women who are willing to participate in the study.

ITT **and** Effectiveness analysis

**Randomization of Participants (n= 810)**

**Informed Consent and**

**Baseline Data Collection**

**Participants’ Recruitment Procedure**

**Design and development of intervention**

**Inclusion Criteria:**

-Women in reproductive age group

-Women who are physically, mentally capable to provide informed consent and can follow intervention provided without any support

-Willing to participate and give data to the researcher.

**Exclusion criteria:**

- Participant who has already attended another intervention program.

- Participants who cannot stay until the intervention is completed/ moveable participants during intervention time

**Intervention group (n= 405)**

- Welcome message,
- Health education
- Brochures and posters
- Perception assessment and positive feedback
- Counseling healthy behavior plan
- continuous follow up

**Control group (n=405)**

- Usual care (services)
- Welcome message
- No continuous follow up

Phase 2 follow up assessment at the end of 3^rd^ and 6^th^ month

**Main outcome:** Screening Uptake **Secondary outcomes:** Increased knowledge, attitude and intention to screening

# Fig. 3 Participants Flow Chart

- - 1. **Method of assignment to study groups**

### Randomization

Randomization will be carried out using a computer program by the investigators. The different kebeles will be alphabetically coded (A, B, C, D and so on) and participants attached to each kebele will be given numerical codes (for example, participants in kebele Y will be numbered Y001, Y002, Y003 and so on. Participants in the randomized controlled trial will be assigned 1:1 to the intervention and control arms under restricted randomized design after informed consent and collection of baseline data. The allocation sequence will be generated and released to the interventionist on a case-by-case basis by another independent department specializes in generating research random sequence. Interventionist, data collectors, statistician are not the same persons. Interventionists also acknowledge all those contacted are in the intervention arm. But anonymous responses will be entered into the database by a person unconnected with the project.

## 3.6. Study Variables

**3.6.1. Dependent variables**

- Breast screening behavior/ uptake (breast self-examination, mammography use, clinical exam)
  - 1. **Predictor variables: (modifying factors, experience and perceptions)**
- **Socio demographic**, socio-psychological and structural characteristics ( age, marital status, religion etc., general knowledge about breast cancer and screening, health motivation/values)
- **Socio-economic variable:** income, occupational status, wealth index
- **Past behaviors related to breast cancer and experience of screening (**knowing status of partner, screening experience).
- **Perceived susceptibility** to breast cancer
- **Perceived severity** of breast cancer
- **Perceived benefit (response efficacy)** of screening in relation to attitude towards cancer treatment, belief for treatment
- **Perceived barrier** of uptake of screening ( fear of being cancer positive, fear of discrimination and stigma, perception of confidentiality, previously knowing the provider, time to think over for readiness, perceived knowledge about the service, perception about non acceptance of accompany)
- **Self-efficacy** to have screening and to live with breast cancer.
- **Cues to actions:** Facilitating and triggering a women to uptake of screening
- **Distal variables** (factors emerged from qualitative parts)

**Constructs for qualitative study:**

- Facilitating for and barriers of screening
- Existing and cultural knowledge for breast cancer and its screening
- Nature and reason of uptake of screening
- Women’s rational decision in undergoing breast screening.
- Irrational ways or defense mechanisms/perceived
- Worrying issues

**3.6.3. Outcome measures:**

Outcomes will be compared between intervention and control arms, and between different time points of each arm. The primary outcomes include breast cancer screening behavior/intention (mammography use, breast self-examination and breast clinical exam), secondary outcomes include increased awareness for breast cancer and its screening and developing health motivation. Another outcome is, not a must, community based intervention mechanism using HBM constructs effectiveness. The outcome for qualitative part will be measured with respect to constructs of health belief model and anomalies treated accordingly. If anomalies are there, they will be used in questionnaire amendments to be included in quantitative and treated as distal factors in the conceptual framework.

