## Data Analysis

Qualitative data will be analyzed by Atlas ti.7 software and use narration and direct quotation. For quantitative, analysis at baseline**, e**quivalence of two arms will be analyzed at baseline. The equivalence will be analyzed by using Mann- Whitley U test, Chi-square test, T-test or ANOVA.

**Analysis of intervention outcomes:** Consolidated standards of reporting trials (CONSORT standards) will be followed for reporting in this study [79]. For intervention arm and control arm comparison, indicators of rates of breast screening, breast self-examination and/or breast clinical exam at baseline, after three months and at the end of six months will be compared by using Chi-square and T-test. And logistic regression model will be used for predicting independent predictors of breast cancer screening behavior.

**Intention-to-treat (ITT):** Outcome will be analyzed under the basis of ITT. First, the principles of ITT will be applied to test the effects of attrition [80], which means that all participants who have been randomized will be included in the analysis. Missing endpoints will be imputed by using the Expectation- Maximization (EM) algorithm. To gauge the robustness of the outcomes, this analysis will be repeated while using Multiple-Imputation approach. Second, propensity score analysis will also be used. By using logistic model (1 for screening uptake and 0 for not) to predict the probability of be in breast screening behavior. And then use the predicted variable to replace the attrition of dummy variable.

Analysis of intervention mechanism in correlation analyses between each aspect of participants’ community based intervention adoption/use behaviors (e.g. frequency of breast screening by mammography, breast self-examination and/or clinical exam) and effectiveness of the intervention will be performed. A causal path model will be built according to correlation analyses results and related theories. And a path analysis will be subsequently conducted so as to calculate the residual path coefficient and determination coefficient, define causal relationships between different variables, and thus explore intervention mechanism of the community based intervention.

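### Intention is part of the primary outcome in section 3.6.3 but secondary in Figure 3, and the protocol never fixes how the three screening methods combine or which follow-up is primary

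*Protocol*

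**What the plan says.** The protocol describes its main outcome in four places.

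- **Section 3.6.3, Outcome measures:** "The primary outcomes include breast cancer screening behavior/intention (mammography use, breast self-examination and breast clinical exam"). It continues: "secondary outcomes include increased awareness for breast cancer and its screening and developing health motivation". Intention is not in that secondary list. The section also plans comparisons between arms and between time points within each arm.
- **Figure 3, Participants Flow Chart:** the main outcome is screening uptake alone. The secondary outcomes are "Increased knowledge, attitude and intention to screening". The schedule is "follow up assessment at the end of 3^rd^ and 6^th^ month", with neither visit singled out.
- **Section 3.6.1, Dependent variables:** "Breast screening behavior/ uptake (breast self-examination, mammography use, clinical exam"). Intention does not appear, and no rule is given for combining the methods.
- **Section 3.9, Data Analysis:** the arms are compared on "indicators of rates of breast screening, breast self-examination and/or breast clinical exam at baseline, after three months and at the end of six months", by chi-square and t-test. In the paragraph on attrition and propensity scores, uptake is coded as binary: "By using logistic model (1 for screening uptake and 0 for not"). Which method or combination earns the 1 is not stated.

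Section 3.5.1 gives the only significance level in the protocol: 5%, two-sided, with 80% power, for one pair of proportions (77.6% and 87.6%). The 77.6% is the share of women with knowledge of breast self-examination.

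**The concern.** Intention and behaviour are different constructs. The intervention is three months of education meant to motivate women to be screened, so stated intention could rise without any more women being screened. Under section 3.6.3 that rise could be reported as a primary result; under Figure 3 it could not. Someone writing the analysis plan could not tell which passage governs.

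The same looseness applies to the methods and the visits. With a plural primary outcome, three methods, no combining rule and two follow-ups treated alike, the method or visit that looks best could be called primary once the data are known. A single 5% comparison, which is what the sample size provides for, would then no longer describe the trial's real chance of a false-positive claim.

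**Working it through.** **1. The passages side by side**

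| Place | Primary or main | Intention | Methods combined? | Primary visit named? |
|---|---|---|---|---|
| 3.6.3 | behaviour/intention, plural outcomes | primary | not stated | no |
| Figure 3 | screening uptake | secondary | not stated | no |
| 3.6.1 | behaviour/uptake | absent | not stated | no |
| 3.9 | rates of screening | not named in the arm comparison | and/or wording | no |

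Intention cannot be both primary and secondary, so the first two rows conflict. The last two columns hold no answer in any row.

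**2. What the sample size covers**

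Inputs from section 3.5.1: π0 = 0.776, π1 = 0.876, two-sided α = 0.05, power 80%, design effect 1.5, 10% added for non-response.

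The stated 245 per arm is reproduced by the pooled two-proportion formula with continuity correction:

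- Mean proportion = 0.826, so 2 × 0.826 × 0.174 = 0.2874.
- π0(1−π0) + π1(1−π1) = 0.1738 + 0.1086 = 0.2824.
- n = (1.96 × √0.2874 + 0.8416 × √0.2824)² / 0.10² = 224.4, so 225.
- With correction: (n/4) × [1 + √(1 + 4/(n × 0.10))]² = 244.0, so **245**.
- 245 × 1.5 = 367.5, so 368; 368 × 1.10 = 404.8, so **405** per arm.

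The formula as printed in 3.5.1 gives 218 with its own numbers, so 245 evidently came from the corrected formula. Either way, the calculation is for one comparison of one proportion at 5%.

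**3. Error rate if the outcomes were tested separately**

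Assumptions, none of which the protocol states: each test is run at two-sided 5%, and any one significant result counts as success. Under independence the family-wise error is 1 − 0.95^k.

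- One composite at two visits, k = 2: 1 − 0.95² = 9.8%.
- Three methods at one visit, k = 3: 1 − 0.95³ = 14.3%.
- Three methods at two visits, k = 6: 1 − 0.95⁶ = **26.5%**.

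The same women answer about related behaviours, so the tests would be correlated. Simulating six equally correlated two-sided z tests (400,000 draws, correlations assumed) gives:

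| Pairwise correlation | 0.3 | 0.5 | 0.7 | 0.9 |
|---|---|---|---|---|
| Family-wise error | 24.1% | 20.6% | 16.3% | 10.8% |

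**4. What adjustment would cost instead**

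Bonferroni over six tests means α = 0.05/6 = 0.0083. With the same rates and inflation this needs 367 per arm before the design effect; 367 × 1.5 = 550.5, so 551; 551 × 1.10 = 606.1, so 607 per arm against 405 planned. At an effective 245 per arm, power per comparison falls from about 83% to about 61% (no continuity correction). A single primary comparison avoids this.

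**The case against.** A single yes/no uptake variable is a natural reading. Figure 3 has one main outcome, 3.6.1 has one dependent-variable entry with the methods in brackets, section 1.5 has one between-group hypothesis, and 3.9 uses a 1/0 code for uptake and and/or wording that suits a combined measure. Section 3.7 gives learning the effect of the intervention as the reason for the six-month round, and treats month 3 as the end of the intervention. Section 3.9 names no test of intention, and the scales listed in 3.7.1 include none for it. Multiplicity procedures are often left to an analysis plan, which is not at hand here.

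Most of this stands, and it rules out three stronger readings that a reader might infer.

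- **That every method and visit is tested at 5%.** The protocol does not say so. Its only significance level is in the sample size section, and no rule says that any one significant result counts as success.
- **That section 3.9 drops mammography.** It does not name mammography in the arm comparison, but breast screening can cover it, and the mechanism paragraph of the same section speaks of screening by mammography.
- **That the absence of a multiplicity procedure is itself an error.** It could sit in the analysis plan.

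The objection does not remove the conflict over intention between 3.6.3 and Figure 3. Nor does it supply a combining rule or a formal primary visit: the binary code appears only in the attrition paragraph, and the wording of 3.7 is a pointer, not a designation.

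**Conclusion.** The protocol contradicts itself on whether intention is primary, and it does not fix one primary endpoint: the composite is undefined and the primary visit is not formally named. This is a defect of the protocol whatever an analysis plan contains, because such a plan would have to choose between conflicting passages.

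The 26.5% figure, or about 24% to 11% for correlations of 0.3 to 0.9, should not be quoted as the trial's error rate. It shows what the unfixed wording would permit if six separate 5% tests were run and any success counted. If uptake is one composite tested once at 6 months, which the text allows, the error rate stays at 5% and the planned 405 per arm needs no increase for multiplicity. Whether 405 suits that composite is a separate matter, since the assumed control rate is knowledge of self-examination and not uptake of any method.

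**What to change.** Settle the wording before outcome data are seen.

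1. Remove intention from the primary outcome in 3.6.3.
2. Use the same single primary endpoint in 3.6.3, Figure 3 and 3.9, for example uptake of any of the three listed methods (yes/no) at 6 months, compared between arms once at two-sided 5%. Bring 3.6.1 and the binary code in 3.9 into line with it.
3. Make the method-specific rates, 3-month results, within-arm changes, intention, knowledge and attitude secondary, and reconcile the two secondary lists, including awareness and health motivation.
4. State in 3.5.1 whether 77.6% versus 87.6% applies to the endpoint chosen. If it does not, give rates that do and recompute the sample size.

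The cost is wording in the protocol, and in the registry entry if it carries the same text, plus the sample size check in step 4. No extra visits or data collection are needed. The small downside is that method-specific and 3-month results can no longer be called primary.
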